## Abstract

**Background:**

The benefits of live donor kidney transplantation must be balanced against the potential harm to the donor. Well-designed prospective studies are needed to study the long-term consequences of kidney donation.

**Methods:**

The “*LO*ng-term follow-up after li*VE* kidney donation” (LOVE) study is a single center longitudinal cohort study on long-term consequences after living kidney donation. We will study individuals who have donated a kidney from 1981 through 2010 in the Erasmus University Medical Center in Rotterdam, The Netherlands. In this time period, 1092 individuals donated a kidney and contact information is available for all individuals. Each participating donor will be matched (1:4) to non-donors derived from the population-based cohort studies of the Rotterdam Study and the Study of Health in Pomerania. Matching will be based on baseline age, gender, BMI, ethnicity, kidney function, blood pressure, pre-existing co-morbidity, smoking, the use of alcohol and highest education degree. Follow-up data is collected on kidney function, kidney-related comorbidity, mortality, quality of life and psychological outcomes in all participants.

**Discussion:**

This study will provide evidence on the long-term consequences of live kidney donation for the donor compared to matched non-donors and evaluate the current donor eligibility criteria.

**Trial registration:**

Dutch Trial Register NTR3795.

## Background

Renal transplantation is the ultimate treatment for patients with end-stage renal disease (ESRD) [1]. The rise of live donor kidney transplantation has helped to narrow the gap between organ shortage and the number of ESRD patients on the transplant waiting list [2]. The benefits of live donor kidney transplantation, such as pre-emptive transplantation, superior organ quality and increased graft survival are well-known [1]. As a result live kidney donation has increased to one third of all kidney transplantations in the last decade [3]. In our transplant center over fifty percent of the kidney transplantations are performed with a kidney of a living donor. Live donor nephrectomy is performed on healthy individuals who willingly undergo major surgery for the benefit of someone else. Over the years, the discomfort of the operation has been minimalized to minimal invasive procedures in many centers with excellent quality of life [4–6].

The benefits for the recipient must be balanced against the potential harm to the donor. Studies on short-term follow-up show excellent results regarding kidney function, mortality and morbidity [7–10]. Reports have recently been published on increased long-term risk of ESRD [11–13] and increased risk of mortality following live kidney donation [14]. Studies on follow-up of ten years or more of live kidney donors demonstrate that the morbidity and mortality increases with the duration of follow-up and subsequent aging. More importantly, these long-term studies comparing donors with non-donors have contradictory outcomes regarding kidney function, incidence of hypertension, ESRD and mortality detriment to donors. The main reason for these contradictory results is the methodology of the different studies [14–22] which jeopardizes the comparability of donors and non-donors.

Furthermore, the incidence of minor co-morbidities among the general population is increasing and quickly become the standard in the potential Western donor population. This could potentially include an increase of incident co-morbidities among previous donors. The occurrence of some of these co-morbidities takes years to emerge and might be missed during a short-term follow-up. In addition, the shortage of kidney donors has led to an extension of the donor acceptance criteria in the recent years, were donors with co-morbidities such as cardiovascular disease, obesity and higher age are no longer denied for donation [23, 24]. Thus emphasizing the need for long-term follow-up of those who donated, including live kidney donors who donated with pre-existing co-morbidities.

To date most studies have merely focused on medical outcomes, resulting in a paucity of research on long-term psychological outcomes [25]. Current published studies focus mainly on the level of quality of life shortly after live kidney donation, which is high [5, 26–28]. Other outcomes, such as depression and anxiety, as well as the potential positive influence of donation on mental health, are often neglected. Therefore, an interesting question is to which extent the donation has had a positive effect on the psychological well-being of the donor.

The aim of this study is to evaluate long-term consequences after live kidney donation for the donor regarding kidney function, the incidence of hypertension, the incidence of diabetes mellitus, the incidence of fatal and non-fatal cardiovascular events, survival, quality of life and psychological well-being when compared to non-donors, and in addition within the donor population. Donors often do not make the decision to donate based on balancing risks and benefits but rather based on emotional or moral reasons. This makes it crucial to inform donors in a standardized uniform fashion when obtaining informed consent [29]. Determining the long-term impact of living donation on physical and psychological well-being is an essential part of evaluating the current donor eligibility criteria and further developing and expanding the live kidney donation program.

## Methods

### Participants and procedure - live kidney donors

The Netherlands has the highest number of live kidney donor transplantations in Europe spread over eight kidney transplant centers, with an annual living donation rate of 31.0 per million population in 2013 [30]. Over the years the Erasmus University Medical Center has developed the largest live kidney donation program of its country with approximately 140 procedures per year and is the referral center for other transplant centers in the country. In 2014, a total of 397 live kidney donor transplantations were performed in the Netherlands [31]. Thirty-five percent of these procedures were performed at Erasmus University Medical Center. All donors who donated a kidney from 1981 through 2010 at the department of Surgery of the Erasmus University Medical Center or who had their full medical work-up here prior to donation, but donated in another transplant center because of their participation in the national kidney exchange transplant program will be eligible to be included in this study. All donors were screened preoperatively by a nephrologist, transplant surgeon, anesthesiologist, and social worker and underwent imaging by renal angiography, magnetic resonance imaging or computerized tomography scan. Since 1981, data on pre-donation characteristics such as prior medical history, medication use, BMI, as well as blood and urine analysis regarding kidney function have been collected. Furthermore, consecutive donors included in two randomized controlled trials on surgical techniques between 2001–2004 and 2008–2010 [4, 32, 33] have completed questionnaires on quality of life pre-donation and at set times after the procedure, using the SF-36 questionnaire and EuroQoL questionnaire. Donors are monitored annually on their kidney function by blood- and urine analysis, blood pressure, weight and other current medical issues at the department of Nephrology of the Erasmus University Medical Center or another hospital, or by their general practitioner. Up to 2011, this database comprises 1092 live kidney donors. Approval of the Medical Ethical Committee was obtained (MEC-2012-519). Pre-donation characteristics on kidney function, BMI, pre-existing co-morbidity and medication of all donors will be updated in accordance with the hospital’s electronic patient system. Mortality will be checked in accordance with the Municipal registry. All donors who are alive will be invited by post to visit the outpatient clinic of one of three hospitals in different regions of the Netherlands for an extensive follow-up appointment, supplementary to their yearly check-up. During the study-visit the donor and study investigators will sign the consent form. During their study-visit, blood and urine will be collected for analysis and donors will undergo two interviews regarding quality of life and their psychological well-being. Furthermore, an ultrasound of their remaining kidney will be performed to measure the size. Participating donors will be reimbursed for their travel costs. Unexpected outcomes will be reported to both the donor and the treating nephrologist, who will initiate subsequent examinations and treatment if needed. The general practitioner and any other treating specialist(s) will be notified if needed. Non-responders will be contacted once again and non-participants will be asked to fill out and return a questionnaire on their medical history and quality of life. In addition, non-participants will be asked to give permission to request recent laboratory results on kidney function and new-onset co-morbidities from their medical records, in order to analyze a potential selection bias. To strengthen our results, we aim for a response of 70 percent or higher. All private data are anonymized by allocating a study number. The coordinating investigators and the principal investigator are the only ones who have access to the coding system. All data will be entered into a database, which is managed by the coordinating investigators. At the end of the study all data will be analysed together with the trial statistician (DR).

### Participants and procedure - non-donors

Non-donors will be selected from the Study of Health in Pomerania (SHIP) [34, 35] and the Rotterdam Study [36, 37], both population based cohort studies to cover the whole age range of our donors.

SHIP is a population-based cohort study initiated in 1997 among inhabitants of West Pomerania in the north-east of Germany. Two main objectives of this study were first to assess prevalence and incidence of common risk factors, subclinical disorders and clinical diseases, and second to investigate the complex associations among these [34, 35]. Data on kidney function, blood pressure, BMI, medication, incidence of cardiovascular disease and diabetes, psychological well-being and quality of life have prospectively been recorded [34]. SHIP comprises two cohorts aged 20–79 years. In our matched study, the first cohort will be used due to the longer follow-up (*n* = 4308). Multiple follow-up examinations of this first cohort were conducted between 1997 and 2015.

The Rotterdam Study is a prospective cohort study that started in 1990 in Ommoord, a neighborhood in Rotterdam, the Netherlands. The study targets cardiovascular, endocrine, hepatic, neurological, ophthalmic, psychiatric and respiratory diseases [36, 37]. As of 2008, 14,926 subjects aged 45 years or over were included. Data such as hypertension, serum creatinine, serum eGFR, cardiac events, mortality, diabetes, quality of life and psychological well-being have prospectively been recorded [37]. The Rotterdam study comprises three different cohorts. We will use the second and the third cohort to select non-donors (*n* = 6943), since these comprises more study parameters compared to the first cohort. Multiple follow-up examinations of these two cohorts were conducted between 2000 and 2012. Given the size of both studies, sufficient data on all study parameters will be available in our reference group.

### Outcome measures

The primary outcome is kidney function in serum creatinine and eGFR (calculated with the CKD-EPI formula) [38]. Secondary outcomes are: diastolic and systolic blood pressure as measured by data scope, incidence of hypertension and incidence of diabetes, incidence of fatal and non-fatal cardiovascular diseases, volume of the remaining kidney in cm^3^ by ultrasound (measured by experienced ultrasonographers), quality of life (measured by EuroQoL and SF-12, that can be extracted from any SF-36 [39, 40]), survival, and psychological well-being (for donors aged 45 years and higher with Hospital Anxiety and Depression Scale (HADS) [41], Center for Epidemiologic Studies Depression Scale (CESD) [42], Pittsburgh Sleep Quality Index (PSQI) [43], and questionnaires on Happiness and Life Satisfaction, and for donors aged 44 years and lower with the Beck Depression Inventory (BDI)) [44]. These outcomes will be compared between groups, but also within the donor cohort.

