### Statistical analysis

All analyses will be performed for each of the completed data sets and the results will be appropriately pooled. For the medical outcomes a conditional linear or Cox regression analysis will be chosen as appropriate for the outcome. For the Cox regression analysis, the proportional hazards assumption will be tested with Schoenfeld residuals. For the psychological outcomes linear mixed-effects models will be used.

For donor subgroup analysis, parametric and non-parametric tests will be chosen as appropriate for descriptive comparisons, Cox regression analysis will be chosen to investigate different outcomes, and mixed models will be chosen for repeated variables, e.g. kidney function and quality of life.

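### The between-group blood pressure comparison takes no account of antihypertensive treatment started after baseline, so a rise after donation may be understated

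*Protocol article*

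**What the plan says.** **Outcome and comparison.** Under Outcome measures, the secondary outcomes include "diastolic and systolic blood pressure as measured by data scope". Incident hypertension is a separate secondary outcome, with no definition given. The section adds: "These outcomes will be compared between groups, but also within the donor cohort".

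**Model.** Under Statistical analysis: "For the medical outcomes a conditional linear or Cox regression analysis will be chosen as appropriate for the outcome". A continuous pressure therefore goes to conditional linear regression. No treatment term, correction or imputation for treated readings is mentioned.

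**Donor follow-up.** Under Participants and procedure - live kidney donors: "Donors are monitored annually on their kidney function by blood- and urine analysis, blood pressure, weight and other current medical issues". The check may take place at a nephrology department, another hospital or the general practitioner.

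**Non-donor follow-up.** Under Participants and procedure - non-donors, the article describes cohort examinations only. For SHIP: "Multiple follow-up examinations of this first cohort were conducted between 1997 and 2015". For the Rotterdam Study: "Multiple follow-up examinations of these two cohorts were conducted between 2000 and 2012".

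**Matching.** Missing data and matching includes blood pressure among the baseline matching variables.

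**Medication data.** Medication is named as a pre-donation item for donors and as a recorded item in SHIP. It is absent from the open-ended list for the Rotterdam Study.

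**The concern.** Antihypertensive treatment is started because pressure is high, and it then lowers the reading that serves as the outcome. If donation raises pressure and donors are checked every year, some of the rise can be found and treated before the study visit. The reading at that visit then shows pressure after treatment. Matching on baseline pressure makes the groups alike at the start but cannot control treatment begun later.

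The likely error is in the reassuring direction. The study is meant to inform donors and to evaluate eligibility criteria. A small or null difference in measured pressure could be read as showing that donation does not raise it, when part of the rise has been treated away. This is a separate matter from how incident hypertension is detected: here the measured level itself is affected.

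**Working it through.** The article states no treatment rate, treatment effect, blood pressure SD or power for this outcome, so there is no figure of its own to reproduce. Every blood pressure input below is an assumption.

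**1. Size of the understatement**

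Observed difference = true rise - (treated share in donors - treated share in non-donors) x treatment effect.

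Assumed: 25% of non-donors and 35-45% of donors treated at the examination; treatment effect 10-15 mmHg systolic.

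| Donors treated | Effect 10 mmHg | Effect 15 mmHg |
|---|---|---|
| 35% | (0.35 - 0.25) x 10 = 1.0 | (0.35 - 0.25) x 15 = 1.5 |
| 45% | (0.45 - 0.25) x 10 = 2.0 | (0.45 - 0.25) x 15 = 3.0 |

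A true rise of 3 mmHg would read 2.0 down to 0.0. A true rise of 2 mmHg would read 1.0 down to -1.0. With equal treated shares the term is zero.

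**2. When the difference vanishes**

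Break-even gap in treated share = true rise / treatment effect. The sign reverses only beyond this gap.

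| True rise | Effect 6 mmHg | Effect 10 mmHg | Effect 15 mmHg |
|---|---|---|---|
| 2 mmHg | 33 points | 20 points | 13 points |
| 3 mmHg | 50 points | 30 points | 20 points |
| 5 mmHg | 83 points | 50 points | 33 points |

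**3. Treatment triggered by the pressure itself**

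Simulation with one million per group. Assumed: untreated mean 135 and SD 18 mmHg in non-donors, the same shifted by the true rise in donors, and only people at 140 mmHg or above eligible for treatment. The cut-off is a modelling device.

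True rise 3 mmHg, 40% of eligible non-donors treated:

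| Eligible donors treated | Overall treated shares, non-donors vs donors | Observed, effect 10 | Observed, effect 15 |
|---|---|---|---|
| 40% | 16% vs 18% | 2.74 | 2.61 |
| 60% | 16% vs 27% | 1.83 | 1.24 |
| 80% | 16% vs 36% | 0.92 | -0.13 |
| 95% | 16% vs 43% | 0.23 | -1.16 |

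The first row shows that equal readiness to treat still loses a little, because more donors cross the cut-off. With a true rise of 5 mmHg, the 80% and 95% rows give 0.22 to 2.56 mmHg and no reversal. Adding the treatment effect back recovers the true rise in every case, but only because the simulation takes that effect as known. Hypertension counted to include treated people still differs by 6.6 points (rise 3) or 11.0 points (rise 5).

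**4. What attenuation does to detection**

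70% of 1092 donors is 764, an upper figure for a response of exactly 70%, since it takes all donors as alive. At 1:4 there are 3056 non-donors. With SD 18, SE = 18 x sqrt(1/764 + 1/3056) = 0.728 mmHg. Ignoring the matching and the re-use of non-donors, two-sided 5% power is 98.5% for 3 mmHg, 78% for 2 mmHg and 28% for 1 mmHg. Attenuation from 3 to 1 mmHg would probably lose the signal.

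**The case against.** **A treated-value rule is analysis-plan content, and the outcome wording only names a device.** Both are fair. The phrase about the data scope says how pressure is read, much as ultrasound is named for kidney volume. A reader might infer a decision to ignore treatment; the text does not say that, and an analysis plan not shown may add a rule. What stands is that the article fixes the outcome and the model family, and that neither accounts for treatment. The choice also determines which follow-up data must be collected.

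**Higher treatment in donors is not stated.** Correct. A reader might infer that non-donors have no comparable care. The article is silent on their routine care, and a donor's yearly check may be with a general practitioner. More treatment in donors is plausible, not documented.

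**Study-visit referral.** The article says "Unexpected outcomes will be reported to both the donor and the treating nephrologist, who will initiate subsequent examinations and treatment if needed". A reader might count this as part of the masking, but it follows the study visit and cannot change the reading taken there. The mechanism rests on the yearly checks before it.

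**Incident hypertension would show the signal.** The Background's aim names incident hypertension, not pressure level, so pressure level is a secondary outcome rather than a stated aim. Incidence is a partial safeguard if treated cases count, which the article does not say. It does not correct the pressure comparison.

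**Pressure under usual follow-up is a legitimate target.** It is, because monitoring accompanies donation. That is a reason to report both comparisons, not to rest everything on a corrected value.

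**Conclusion.** The point holds as a likely bias towards no effect in a secondary outcome. As described, the comparison does not account for antihypertensive treatment started after baseline, and the described follow-up makes more treatment in donors plausible.

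Under the assumed shares and treatment effects, the understatement is 1-3 mmHg. That rests on a gap of 10-20 points in treated share, which the article neither gives nor rules out; a smaller gap gives a smaller bias.

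A reader might go further and infer that the comparison would show lower pressure in donors. The figures do not support this as the expected result. Across the assumed shares in step 1, a true rise of 3 mmHg falls to zero at most, and a rise of 2 mmHg reverses only when the gap exceeds 13 points at an effect of 15 mmHg. The simulated reversals at 3 mmHg need an effect of 15 mmHg and a gap of 20 points or more. Attenuation is the realistic risk.

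**What to change.** 1. Take antihypertensive use at the follow-up examination in donors, SHIP and the Rotterdam Study. Confirm that it is available for the Rotterdam Study; a hypertension variable alone may not separate treated from untreated people.
2. Prespecify a treatment-corrected between-group comparison of systolic and diastolic pressure: either add a constant to treated readings, over a stated range, or use censored regression with each treated reading as a lower bound for underlying pressure. Adjusting for treatment as a covariate is not a substitute, because treatment is a consequence of raised pressure.
3. Report it beside as-measured pressure and the share treated in each group.
4. State that the as-measured comparison alone will not support a conclusion that donation does not raise blood pressure.
5. State whether treated cases count as incident hypertension, so that the two outcomes can be read together.

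**Cost.** Analysis wording, plus one item at the donor visit and in the cohort data requests. If the Rotterdam Study lacks the item, the corrected comparison is limited there. The corrected result depends on an assumed treatment effect, which is why a sensitivity range is needed. No change to clinical care is involved.

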### Missing data and matching

Participants from the Rotterdam Study and SHIP will be restricted from analysis if they would not qualify for live kidney donation based on the following criteria: prevalent diabetes, an eGFR < 60 ml/min/1.73m^2^, and a BMI > 40 (kg/m^2^). To account for the fact that data for covariates at baseline are not complete for all subjects, a multiple imputation approach will be utilized based on the method of chained equations [45]. Using this procedure 10 complete data sets will be created, and for each of the data sets the following steps will be performed: First, donors and non-donors will be 1:4 matched using propensity score matching based on the baseline covariates: age, gender, year of donation/inclusion, BMI, ethnicity, kidney function, blood pressure, pre-existing co-morbidity, glucose level, smoking, alcohol use and highest education degree. Exact matching will be required for gender, ethnicity, existing co-morbidity, and smoking. Progressive radius matching will be performed for age, BMI, kidney function and blood pressure. Each non-donor subject will be allowed to serve as a potential match to more than one donor. If the available data in the control group is insufficient, the target ratio of 1:4 donor:non-donor will be reduced accordingly.

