All these variations might explain the contradictory results. As donors are a highly selected healthy population, comparison to the general population might lead to an underestimation of long-term risks [16]. For this reason, a study on long-term outcome, including baseline data and a well-matched non-donor group, is the design of choice. In the design of our study we tried to adhere to suggestions of authors of these previous studies. The current donor-cohort of our study forces us to use two different population-based cohort studies to form our non-donor group, as no single population-based study incorporating representative individuals with a broad enough age range provided the desired set of parameters. Nevertheless, this design will facilitate in a one to four proportion. Previous studies in our center in the same living donor population have always resulted in a high response [5, 6, 27, 47]. Although a selection bias can never be precluded, analysis of the non-responding group should provide us with an indication of whether the sample is representative. Our study population includes elderly donors and donors with minor co-morbidity. As there is currently little research on these sub-groups, this study should clarify the ambiguities concerning the long-term outcomes in these groups.

With this study we will try to overcome the limitations of previous studies. We aim to assess the long-term consequences of live kidney donation after a decade post-donation. This study will compare donors with a matched group of non-donors, regarding kidney function, kidney-related comorbidity, quality of life and psychological outcomes.

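### Non-donor restriction and matching name neither urinary protein nor baseline mental health, so controls may stay less healthy than the screened donors and donor risk may be underestimated

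*Protocol article*

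**What the plan says.** Under Missing data and matching, members of the two population cohorts are restricted "if they would not qualify for live kidney donation based on the following criteria: prevalent diabetes", followed by "an eGFR < 60 ml/min/1.73m^2^, and a BMI > 40 (kg/m^2". The list ends there.

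The donor side is described under Participants and procedure - live kidney donors: "All donors were screened preoperatively by a nephrologist, transplant surgeon, anesthesiologist, and social worker and underwent imaging by renal angiography" or another imaging method. Since 1981 the pre-donation record has held "prior medical history, medication use, BMI, as well as blood and urine analysis regarding kidney function have been collected".

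A second filter follows the restriction. The propensity score uses age, gender, year and "BMI, ethnicity, kidney function, blood pressure, pre-existing co-morbidity, glucose level, smoking, alcohol use and highest education degree". Gender, ethnicity, existing co-morbidity and smoking must match exactly. Age, BMI, kidney function and blood pressure are matched by progressive radius.

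Outcome measures defines kidney function by serum creatinine and eGFR, and states that the outcomes, including psychological well-being, are compared between groups. Background asks "to which extent the donation has had a positive effect on the psychological well-being of the donor".

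**The concern.** The three-item list is presented as the test of who would not have qualified to donate, yet it is much narrower than the work-up the donors went through. Controls come from general-population cohorts. If health differences that the work-up removed from the donors persist in the controls, and matching does not remove them, the controls do worse for reasons unrelated to donation. Kidney outcomes, cardiovascular events and survival in donors then look more favourable than they should.

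The Discussion recognises this mechanism for unselected comparators: "As donors are a highly selected healthy population, comparison to the general population might lead to an underestimation of long-term risks". Better comparability is the study's main claim over earlier work, so what remains of the gap matters.

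The psychological outcomes face the same problem. Donors were seen by a social worker before donation, and no baseline mental-health variable is named for the controls. A better donor score could reflect who was accepted rather than what donation did.

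**Working it through.** **Step 1: compare the lists.**

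| Item | Donor work-up or record | Non-donor restriction | Matching |
|---|---|---|---|
| Diabetes / glucose | history, blood | yes | glucose in propensity score |
| Kidney function | blood and urine | eGFR below 60 | radius |
| BMI | yes | above 40 | radius |
| Blood pressure | not itemised | no | radius |
| Co-morbidity | history, medication | diabetes only | exact, not itemised |
| Urinary protein | urine analysis on record | not named | not named |
| Mental health | social worker seen | not named | not named |

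Matching covers most rows. The last two rows are covered by neither list. Because the article defines kidney function by creatinine and eGFR, that matching variable does not evidently include urinary protein.

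**Step 2: direction.** A factor that worsens outcome and is commoner in controls than in donors lowers the donor/control ratio. This is the direction the Discussion gives.

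**Step 3: illustrative size.** The article states no figure to reproduce. The usual external-adjustment formula is

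observed ratio = true ratio × [1 + pd(R − 1)] / [1 + pc(R − 1)],

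where pd and pc are the prevalences of the unmatched factor in donors and controls, and R is its risk ratio for the outcome. All three are assumptions, not document figures: pd 0-2%, pc 2-15%, R 1.5-3. The prevalences are those left after restriction and matching.

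- No bias: pd = 2%, pc = 2%, any R gives 1.00.
- Middle case: pd = 0, pc = 5%, R = 2 gives 1 / (1 + 0.05 × 1) = 1 / 1.05 = 0.95.
- Donors not free of the factor: pd = 2%, pc = 10%, R = 2 gives 1.02 / 1.10 = 0.93.
- Extreme: pd = 0, pc = 15%, R = 3 gives 1 / (1 + 0.15 × 2) = 1 / 1.30 = 0.77.

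An assumed true ratio of 1.20 would read 1.20 / 1.05 = 1.14 in the middle case and 1.20 / 1.30 = 0.92 at the extreme. The formula serves ratio outcomes such as mortality or cardiovascular events. It gives no figure for mean eGFR or for psychological scores.

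**Step 4: room for stricter selection.** The pool is 4308 + 6943 = 11,251 before any exclusion. A 1:4 match needs 4 × 1092 = 4368 control places for all donors. At the targeted 70% response, 0.70 × 1092 ≈ 764 donors need 4 × 764 = 3056. These are crude counts; exact matching will make some strata thin.

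**The case against.** The strongest reply is that restriction is only the first of two filters. A control with a recorded co-morbidity that no comparable donor has cannot be matched, so for conditions under that term exact matching works as exclusion. Radius matching also aligns baseline kidney function, blood pressure and BMI. This stands, and it removes part of the gap.

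A reader might infer more than the article supports:

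- **That controls certainly are sicker and donor risk certainly is underestimated.** The matching and the lower end of the range in the working both leave room for no bias.
- **That a history of malignancy goes uncontrolled.** It may fall under the co-morbidity term, and an article may leave the itemisation of that term to the full protocol.
- **That people barred from donating for proteinuria or mental illness stay in as controls.** The article does not say what barred donation at this centre. It says a social worker took part in screening, not that anyone was declined on mental health. Background adds that some co-morbidities no longer lead to refusal.
- **That the Discussion sentence admits a flaw in this design.** It concerns comparison with the general population and is given as a reason for a well-matched control group.

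It is also fair that the article's description of the cohorts lists neither urinary protein nor malignancy, and lists medication only for SHIP, so availability cannot be taken for granted.

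These replies do not settle the two named gaps. Urinary protein could be read into kidney function, but the outcome definition points away from that. Baseline mental health appears under no name, although psychological well-being is compared between groups.

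**Conclusion.** The point holds in a limited form. The stated rule leaves urinary protein and baseline mental health outside both restriction and matching, so some healthy-donor bias may remain. It would make donor risk look smaller, and it may make donors' psychological scores look better through selection.

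The size is unknown. Under the assumed inputs, the observed ratio is between 0.77 and 1.00 times the true one, with 0.95 in the middle case. The upper end of that range is no bias. The lower end requires that no donor carries the factor and that 15% of matched controls do, with a threefold risk. This is a worthwhile and inexpensive improvement to control selection; it does not show that the comparison is invalid.

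**What to change.** 1. Apply to non-donors the centre's own donor-exclusion criteria as far as the two cohorts recorded them, and apply the same list to both groups so that donors accepted under wider criteria are handled consistently.
2. Add urinary protein or albumin to the restriction or matching set where available. Urine analysis is already on the donor record.
3. For psychological and quality-of-life outcomes, add baseline psychiatric history or psychotropic medication to the matching or the adjustment.
4. Where a cohort lacks an item, show the result with and without it.
5. Describe between-group psychological and quality-of-life differences as associations unless baseline values are available. The article describes pre-donation SF-36 and EuroQoL data only for donors in the two surgical trials (2001-2004 and 2008-2010).

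The cost is a request to the cohorts for extra variables and some loss of eligible controls from the 11,251. The reuse of controls and the reduced matching ratio that the plan already allows can absorb that loss. No new donor procedure is needed.
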